### Randomization

Patients are randomized via a randomization program, using a computer-generated list of random numbers. Block randomization will be used (no stratification) to assure approximately equal numbers in both groups. Concealment of randomization allocation is guaranteed by the fact that only after written informed consent, the trial manager obtains the randomization allocation from the randomization program and sends it to the gynecologist.

### Intervention versus usual care

#### Usual care

The control group receives follow-up care according to Dutch guideline [2] . This guideline proposes follow-up visits every 3–4 months during the first and second years, every 4–6 months during the third year, and every 12 months during the fourth and fifth years after the end of treatment irrespective of stage and grade [2], resulting in a total of 10–13 visits in five years.

#### Intervention

In the intervention group, the follow-up schedule will be limited to four follow-up visits at 3, 12, 24, and 36 months, under the specific condition that patients have easy and prompt access to care (specialized nurse of gynecologist) if symptoms or questions occur. The content of the follow-up visits will be similar for both groups. In both arms a Survivorship Care Plan, including signs of recurrence, will be provided [33]. This Survivorship Care Plan is personalized based on information that is completed in the randomization form and is emailed as a pdf file to the patient’s caregivers upon randomization.

### Patient and medical outcomes

During the study the following outcomes will be assessed using clinical research forms.

*Patient-related outcomes* include date of birth, other malignancies during the past five years, WHO performance status, weight, height, co-morbidity, menopausal status

*Conduct of preoperative investigations*, including CT or X-ray of the chest, CT or MRI of the abdomen and pelvis, and Ca-125.

*Surgery-related measures* include date of surgery, date of hospital discharge, type of surgery, blood loss, transfusion, complications of surgery, if the patients were in intensive or medium care, if there was a re-intervention for complications

*Pathology investigations* include histology, FIGO stage, FIGO grade, size of the tumor, myometrial invasion, minimal distance between the tumor and the serosa, LVSI.

*Follow-up measures* include date of follow-up visit, being a regular or extra visit, performance status, disease status, healthcare use (gynecologist, oncology nurse), investigations (CT or X-ray of the chest, CT or MRI of the abdomen and pelvis, PET scan, echo, Ca-125)

*Recurrence measures* include symptomatic/asymptomatic recurrence, localization, date, and new treatment.

*End of study measures* include date lost to follow-up, reasons loss to follow-up, and date and cause of death.

*Healthcare use* comprises consults with the specialist, the (specialist) nurse, and the primary care physician, hospital admissions, length of hospital stay, and diagnostics (X-ray, CT, MRI, PET scans, echo, Ca-125).

*Cost-prices* will be obtained from guideline on cost research from the CVZ [34].

### Patient-reported outcomes

We will use existing validated instruments to measure the patient reported outcomes that we hypothesized to be affected by the follow-up visits.

*Patient satisfaction with follow-up care* will be assessed using the Dutch version of the Patient Satisfaction Questionnaire III of which the psychometrics have been assessed in a Dutch oncologic sample [35]. This includes three aspects of healthcare: technical competence (ten items); interpersonal aspects (14 items); and access to care (12 items). The questionnaire can be used as a one-dimensional model, which will be used as the main outcome (PSQ total score).

*Overall quality of life* will be assessed using the EQ-5D [36], a standardized instrument which provides a descriptive profile and a single index value for health status. The measure will be used for the economic evaluation, as it can be used to compute QALYs.

*Cancer-specific HRQoL* will be measured using the EORTC-QLQ-C30 [37]. Much of the content of the questionnaire is appropriate for extended monitoring of health status, including scales assessing physical, role, cognitive and emotional functioning, fatigue and sleep problems, and overall health and QoL.

*Tumour-specific complaints* will be measured using a condition-specific supplement, the EORTC-QLQ-EN24 [25]. The module assesses lymphedema, urological symptoms, gastrointestinal symptoms, body image, sexual/vaginal symptoms, back/pelvic pain, and chemotherapy side effects.

*Worry*, including fear of recurrence, will be assessed using a module from the validated IOCv2 [38] questionnaire. The module consists of six questions including items about worry about the future, worry about health because of the cancer, and worry about a recurrence. This module is a concise measure to assess fear of recurrence and worry.

*Anxiety and depression* will be assessed using the Hospital Anxiety and Depression Scale (HADS), an often used and validated scale in this population [39, 40].

*Satisfaction with information* will be measured using the EORTC-INFO25 module [41]. This questionnaire aims to evaluate the (satisfaction with) information received by cancer patients on different areas of the disease, diagnosis, treatment, and care. The questionnaire contains the following scales: (1) information about the disease; (2) information about medical tests; (3) information about treatment; (4) information about other services—and the following single items: (1) written information; (2) information on CD or tape/video; (3) satisfaction with the amount of information; (4) desire for more information; (5) desire for less information; and (6) helpfulness of information.

*Healthcare use* will also be assessed by asking the frequency of contact with the primary care physician and medical specialist. We will also ask the patient how often these visits were related to cancer. In addition, we will assess how often the patients used additional care services (e.g. psychologist, rehabilitation course, physiologist).

*Co-morbidities at the time of questionnaire completion* will be measured using the Self-administered Comorbidity Questionnaire (SCQ) [42]. Patients will be asked to identify co-morbid conditions developed in the past 12 months. The adapted SCQ lists 14 medical conditions (with the option to list up to three additional conditions).

Additional measures include demographic and socioeconomic variables such as age, education, marital status, and employment status.

### Non-participation evaluation

Patients who do not want to participate in the trial are asked to complete a single questionnaire. Questions include demographics, worry (including fear of recurrence), illness perceptions, and satisfaction with care. For patients who provide informed consent to assess healthcare use, hospital healthcare use (number of visits to the gynecologist and the specialized nurse) will be registered.

### Healthcare provider evaluation

Since the satisfaction of the healthcare provider is also of interest in this project, we will assess the satisfaction of the specialists with the follow-up schemes using a short questionnaire.

### Sample size

The power calculation is performed on the first primary outcome “satisfaction with follow-up care.” The maximal difference between the groups that we find acceptable (non-inferiority margin) is 6 points (< 0.5 SD) on a scale from 0 to 100, with a standard deviation (SD) of 14.3 by [35], based on the rule of thumb as supposed for the EORTC_QLQ-C30 questionnaire [43]. Therefore, with alpha 0.05 and beta 0.80 we need a sample size of 180 (90 per study arm). In this sample size we assume that 30–50 centers will participate and as a consequence we adjusted the number needed in the analysis to account for the clustering of patients within hospitals. With an expected loss to follow-up of 20% and patient who die (16%) over five-year follow-up we need to include 282 patients. Assuming that 60% of the patients will participate, we need 470 eligible patients. In the Netherlands, 450 patients per year meet the inclusion criteria. Since not all hospitals will start inclusion at the same time, we expect an inclusion period of 2.5 years.

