### Design

A national multicenter (non-inferiority) RCT among 282 endometrial cancer survivors will be conducted. Patients will be randomized 1:1 in the intervention or control group. Since differences in outcomes between groups are expected to be most pronounced within the first three years of follow-up and the largest cost-saving is achieved within three years, we will evaluate this study in a two-step approach, with an evaluation after one, three, and five years. After five years, the follow-up according to the guideline ends. Patients in both arms receive a Survivorship Care Plan, with information on symptoms which would necessitate a consultation.

Doctors and patients cannot be blinded for intervention or control group assignment. A questionnaire will be sent to all patients at baseline (after primary treatment), and 6, 12, 36, and 60 months later. The baseline questionnaire will be assessed before the intervention under study, that is the different follow-up schedules, starts. Healthcare use, recurrences, survival, and costs will be assessed after three and five years. A schedule of the study is presented in Fig. 1. Healthcare professionals will receive a questionnaire at the end of the study. In addition, a non-participation study will be performed registering hospital healthcare use and assessing patient-reported outcomes using a questionnaire. Medical Ethics approval will be obtained before the start of this project.

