### Statistical analysis

Data will be analyzed after one, three, and five years of follow-up. All patients will be included in the analyses and all patients will be analyzed according to the arm to which they were assigned (intention-to-treat). In addition, per protocol analyses will be conducted including patients who received follow-up care as intended in the trial arms. Intention-to-treat and per-protocol analyses are both important in non-inferiority trials. Data will be analyzed using descriptive statistics, linear, and logistic regression analyses. Primary outcome is satisfaction with follow-up care over three-year follow-up. The primary outcome will be analyzed one-sided. Secondary outcomes will also be analyzed as non-inferiority using 0.5 SD as a non-inferiority margin, but will be tested two-sided.

Multilevel multivariate linear and logistic regression analyses will be conducted for continuous and dichotomous outcomes, respectively. Analyses will include relevant pre-defined covariates to improve the power. Differential effects by fear of recurrence will be evaluated by adding the interaction term (group*moderator) to the model. We will carry out repeated measures analyses using multilevel linear mixed models, which accounts for the intra-patient dependency of the repeated measures. Missing outcomes will be assumed missing at random (MAR). An advantage of multilevel linear mixed models is that all patients can be included in the analyses, regardless of whether they have been missing some follow-up measurements. All tests will be considered significant if *p* < 0.05. Clinically meaningful differences will be determined with Norman’s “rule of thumb,” whereby a difference of > 0.5 SD indicates a threshold of discriminant change in health status scores of a chronic illness [43]. If we have the baseline data of a patient, we will include this patient in the analysis.

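### The sample size is said to allow for clustering within hospitals, but 180 and 282 follow with no such allowance at one-sided 0.025; at one-sided 0.05, the alpha that the analysis section implies, 180 gives about 88% power, not 80%

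*Protocol article*

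**What the plan says.** All of this is in the protocol article.

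- **Sample size, inputs.** The "non-inferiority margin) is 6 points (< 0.5 SD) on a scale from 0 to 100", "with a standard deviation (SD) of 14.3".
- **Sample size, result.** "with alpha 0.05 and beta 0.80 we need a sample size of 180 (90 per study arm"). The sidedness of alpha is not given here.
- **Sample size, clustering.** With 30 to 50 centres assumed, "as a consequence we adjusted the number needed in the analysis to account for the clustering of patients within hospitals". No intracluster correlation (ICC), cluster size or design effect is shown.
- **Sample size, attrition.** Loss to follow-up of 20% and deaths of 16% lead to 282 enrolled.
- **Design.** "Patients will be randomized 1:1 in the intervention or control group".
- **Randomization.** "Block randomization will be used (no stratification").
- **Statistical analysis.** "The primary outcome will be analyzed one-sided". Later in the section: "All tests will be considered significant if" p is below 0.05. Read together, these imply a one-sided primary test at 0.05. The value 0.025 appears nowhere.

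**The concern.** The paragraph claims an allowance for clustering, but its own inputs return both printed totals without one. If the allowance was made, it must sit in the gap between a one-sided 0.05 calculation and 180. It then resembles the inflation used when whole hospitals are randomised, which is not this design.

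Two things are at stake. The first is the type I error for which this non-inferiority trial was sized: 0.025, or the 0.05 that the analysis section implies. The second is whether 80% is the power that 180 analysable patients deliver. The label on 0.80 adds to the confusion, since a beta of 0.80 would mean 20% power.

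**Working it through.** **Inputs from the article.** Margin 6, SD 14.3, power 0.80 (printed as beta), alpha 0.05 with sidedness unstated, 1:1 allocation, 30–50 centres, attrition 20% + 16%.

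**Assumptions not in the article.** True difference 0; ICC values as stated below.

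**Formula.** n per arm = 2 × (SD/margin)² × (z for alpha + z for power)². Here 2 × (14.3/6)² = 11.36.

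**1. Reproducing 180 and 282: one-sided 0.025 (the same as two-sided 0.05)**
- 11.36 × (1.960 + 0.8416)² = 89.17, so 90 per arm and 180 in all.
- 180/(1 − 0.20 − 0.16) = 180/0.64 = 281.25, so 282.
- Applying the two attrition rates in sequence gives 180/(0.80 × 0.84) = 267.9, so 268. That does not match, so the two rates were added.

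Both printed figures are returned, and neither step leaves room for a clustering factor.

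**2. One-sided 0.05**
- 11.36 × (1.645 + 0.8416)² = 70.24, so 71 per arm and 142 in all (142/0.64 = 221.9, so 222 enrolled).
- 180/142 = 1.27. If 180 came from this alpha, it contains a factor of that size.
- Setting 1 + (m − 1) × ICC = 1.27, the implied ICC depends on the number of centres and on which total is used for the cluster size m:

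| Centres | m from 180 | ICC | m from 142 | ICC |
|---|---|---|---|---|
| 30 | 6.0 | 0.054 | 4.73 | 0.072 |
| 40 | 4.5 | 0.076 | 3.55 | 0.105 |
| 50 | 3.6 | 0.103 | 2.84 | 0.145 |

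The range is roughly 0.05 to 0.15. One combination that returns the printed figure is 40 centres with an assumed ICC of 0.10: 1 + 2.55 × 0.10 = 1.255, and 71 × 1.255 = 89.1, so 90 per arm.

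**3. Does this design need such a factor?**

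The expression 1 + (m − 1) × ICC applies when all patients in a hospital receive the same arm. Here patients are randomised individually, so a shared hospital effect falls on both arms and largely cancels. This was checked by simulation: 180 patients spread over 30 or 46 centres, unstratified 1:1 randomisation, assumed ICC 0.05 or 0.10, 6,000 runs each. The variance of the treatment difference, relative to no clustering, was:
- 0.98 to 1.02 for the simple difference in means;
- 0.95 to 1.01 for an estimate that models hospital.

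The simulation error of such a ratio is about √(2/6000) = 0.018, so there is no inflation to correct.

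**4. Power with 90 per arm**
- Standard error = 14.3 × √(2/90) = 2.132, and 6/2.132 = 2.815.
- One-sided 0.025: 2.815 − 1.960 = 0.855, power 80.4%.
- One-sided 0.05: 2.815 − 1.645 = 1.170, power 87.9%.

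**The case against.** The best defence starts from the alpha that the analysis section implies. At one-sided 0.05 there is room in 180 for an adjustment, the sentence refers to the number needed in the analysis (180 rather than 282), and 40 centres with an ICC near 0.10 return the figure. An article may leave the ICC to the full protocol. The unadjusted match in step 1 also holds only for the normal-approximation formula; a t-based calculation gives 182. Some margin for clustering in an unstratified multicentre trial is cautious rather than harmful.

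Much of this stands. The match at one-sided 0.025 is striking, but it does not prove that no adjustment was made. A reader might infer that the clustering sentence is simply false. The article does not settle that, because the sample size paragraph leaves sidedness open and the analysis section points to 0.05. The absence of an ICC is not itself the error.

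The defence still does not make the paragraph correct. If the adjustment is present, it corrects for an inflation that individual randomisation does not produce, and the power is about 88%, not 80%. Variation of the treatment effect between hospitals could be a different justification. To turn 142 into 180 it would need a between-hospital SD of about 6 to 8 points, at least as large as the margin, and the article claims nothing of the kind.

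**Conclusion.** The stated basis of the sample size is wrong as written on both readings of alpha.

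- **One-sided 0.025:** the clustering adjustment is absent from 180 and 282, and the trial was sized at a stricter level than the analysis section implies.
- **One-sided 0.05:** 180 contains a factor of about 1.27 that this design does not need for a shared hospital effect, and the 80% power is understated.

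The article does not show which reading applies. The power figures assume a true difference of 0 and an SD of 14.3; the finding of no inflation assumes a hospital effect common to both arms.

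A reader might also infer that a design effect should be added on top of 180 and that the trial is therefore too small. The article does not support this: patients are randomised individually, and 180 analysable patients give 80.4% or 87.9% power. This is a minor correction to the stated basis, not a shortage of patients.

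**What to change.** Keep 282. Establish from the record of the calculation which alpha was used, then:

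1. State the sidedness of alpha in Sample size and make it agree with the primary test in Statistical analysis.
2. If it is one-sided 0.025, delete the clustering sentence and state that threshold for the primary test in Statistical analysis. Changing Sample size alone would create a new contradiction.
3. If it is one-sided 0.05, either restate the power of 180 analysable patients as about 88% with no clustering allowance, or show the ICC, cluster size and factor and justify them for an individually randomised trial.
4. In either case, call 0.80 the power, not beta.

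The cost is one reworded paragraph and, under item 2, one added threshold. Enrolment, visits and data collection do not change.

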### Statistical analysis

Data will be analyzed after one, three, and five years of follow-up. All patients will be included in the analyses and all patients will be analyzed according to the arm to which they were assigned (intention-to-treat). In addition, per protocol analyses will be conducted including patients who received follow-up care as intended in the trial arms. Intention-to-treat and per-protocol analyses are both important in non-inferiority trials. Data will be analyzed using descriptive statistics, linear, and logistic regression analyses. Primary outcome is satisfaction with follow-up care over three-year follow-up. The primary outcome will be analyzed one-sided. Secondary outcomes will also be analyzed as non-inferiority using 0.5 SD as a non-inferiority margin, but will be tested two-sided.

Multilevel multivariate linear and logistic regression analyses will be conducted for continuous and dichotomous outcomes, respectively. Analyses will include relevant pre-defined covariates to improve the power. Differential effects by fear of recurrence will be evaluated by adding the interaction term (group*moderator) to the model. We will carry out repeated measures analyses using multilevel linear mixed models, which accounts for the intra-patient dependency of the repeated measures. Missing outcomes will be assumed missing at random (MAR). An advantage of multilevel linear mixed models is that all patients can be included in the analyses, regardless of whether they have been missing some follow-up measurements. All tests will be considered significant if *p* < 0.05. Clinically meaningful differences will be determined with Norman’s “rule of thumb,” whereby a difference of > 0.5 SD indicates a threshold of discriminant change in health status scores of a chronic illness [43]. If we have the baseline data of a patient, we will include this patient in the analysis.

The cost-effectiveness analysis will be performed from a healthcare perspective with a time horizon of 36 months and will be expressed as the incremental cost per QALYs (based on the EQ-5D) and the incremental costs per satisfied patient. Based on results up to 36 months, five-year cost-effectiveness results will be estimated. Patient adherence to the reduced follow-up schedule will explicitly be addressed in the cost-effectiveness analysis. A budget impact analysis will be performed according to the ISPOR guidelines [44]. The budget impact analysis addresses the financial stream of consequences related to the implementation of and compliance with the reduced follow-up scheme to assess affordability. The budget impact will depend on both the cost-savings due to reduced follow-up visits, the uptake by specialists, adherence of patients as well as potential cost increases, e.g. at the level of the primary care physician.

Results of the trial will be published in scientific journals and communicated to the patients via patient organizations.

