**Methods:**

In this multicenter randomized controlled trial, patients diagnosed in the Netherlands with stage 1A and 1B low-risk endometrial cancer, for whom adjuvant radiotherapy is not indicated (*n* = 282), are randomized. Patients allocated to the intervention group receive four follow-up visits during three years. Patients allocated to the control group receive 10–13 follow-up visits during five years, according to the Dutch guideline. Patients are asked to fill out a questionnaire at baseline and after 6, 12, 36, and 60 months. Primary outcomes include patient satisfaction with follow-up care and cost-effectiveness. Secondary outcomes include healthcare use, adherence to schedule, health-related quality of life, fear of recurrence, anxiety and depression, information provision, recurrence, and survival. Linear regression analyses will be used to assess differences in patient satisfaction with follow-up care between intervention and control group.

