Current evidence provides a multitude of reasons that support reduction of standard follow-up visits. First, there is no survival benefit in the detection of asymptomatic recurrences at routine follow-up, compared with symptomatic recurrence or interval detection [4, 5, 8, 16–18], probably because the recurrence rate of early-stage endometrial cancer survivors is low (3%) and because most recurrences (70%) present with symptoms [5]. The majority (70–100%) of the recurrences occur within three years [5]. Second, side-effects from treatments are found in only 6% of the stage 1 patients who received surgery (hysterectomy and salpingo-oophorectomy) alone [2, 19]. Third, follow-up visits evoke distress around the time of the visits [15, 17, 20–22]. Finally, alternative follow-up schedules in other cancer populations do not show decreased patient satisfaction or health-related quality of life (HRQoL) [23, 24]. At the same time, there are reasons to retain some follow-up care, including that follow-up is beneficial for patients for reassurance [15, 21, 25], to provide support for psychosocial, physical, and sexual problems [2, 3, 24], and to provide information [26] and tertiary prevention care [27].

These findings suggest that most early-stage endometrial cancer patients do not need intensive follow-up to detect recurrences, improve survival, or discuss consequences of treatment. However, patients may need *some* follow-up to detect information needs and provide psychosocial counseling. Therefore, a reduced follow-up schedule for low-risk, early-stage endometrial cancer patients should focus on eliminating unnecessary care, which is expected to result in decreased patient worry around visits, prevent wrong patient expectations, and save healthcare costs. At the same time, a minimal number of follow-up visits is needed to support necessary patient counseling and information provision [8–10].

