## Methods/Design

### Objectives and hypotheses

The aim of this study is to compare a reduced follow-up schedule of four visits in three years among low-risk, early-stage endometrial cancer survivors, with the schedule according to the current Dutch guideline that includes 10–13 visits in five years. Primary outcomes include patient satisfaction with follow-up care and costs-effectiveness from the healthcare perspective. Secondary outcomes include healthcare use, adherence to the indicated follow-up protocols, reasons for non-adherence, HRQoL, worry including fear of recurrence, anxiety and depression, satisfaction with information provision, healthcare providers’ satisfaction with follow-up schedule, time till recurrence, and survival.

We hypothesize that endometrial cancer patients in the intervention arm of the study are not less satisfied with the follow-up care and do not report worse HRQoL, fear of recurrence, anxiety, depression, and information provision satisfaction. We furthermore hypothesize that healthcare use and associated costs will be lower in the intervention arm, resulting in a cost-effective intervention. More precisely, we expect that by reducing the follow-up schedule from 10–13 to four visits, the costs of these visits will be saved, although some substitution might occur to care by the specialist, specialized nurse, or general practitioner. From a healthcare perspective, we expect this alternative follow-up schedule will save costs.

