## Discussion

Although the current guidelines in the Netherlands describe five years of hospital-based follow-up for women after their treatment for endometrial cancer, hardly any scientific evidence exists to support this timely and expensive practice which involves increasing resources due to the growing number of cancer survivors. Therefore, a critical evaluation of follow-up care for endometrial cancer survivors is needed. The current landscape of evidence predominantly focuses on transitioning follow-up care to nurses or primary care physicians [45]. However, we hypothesize that reducing the frequency of follow-up care would result in a higher cost-effectiveness through retaining levels of satisfaction and outcomes, while decreasing the costs of follow-up care. Outcomes of our trial may therefore evoke a new framing of the issue of follow-up care, by shifting the focus from transitioning care to eliminating unnecessary care, without disregarding a minimal level of follow-up care that is needed to provide adequate information, psychosocial support, and tertiary prevention [15, 21, 25]. Although Survivorship Care Plans did not increase satisfaction with information and care in a previous trial [30, 31], we expect that Survivorship Care Plans support symptom monitoring, thereby limiting the need for additional follow-up visits to detect symptomatic recurrences.

Patients who do not agree to participate in the trial may have higher needs regarding follow-up care and, for instance, higher levels of psychological distress. If our non-participation study shows differences between participants and non-participants, the results of the study may not be generalizable to the full population of interest. In light of this potential result, individualized follow-up care may be a viable solution, by tailoring the number of follow-up visits based on patient preferences and (clinical) characteristics. On the other hand, if participants of the trial seem representative of the target population and a reduced follow-up schedule results in a similar patient satisfaction at lower costs, the current guideline will be adapted and the reduced schedule will be implemented throughout the Netherlands. Furthermore, a reduced follow-up schedule may be applicable to other cancer types and practices outside of the Netherlands.

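### The 0.5 SD non-inferiority margin is applied to every secondary outcome, including recurrence and survival, for which it is undefined or far too wide

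*Protocol article*

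**What the plan says.** The Statistical analysis section of the protocol article sets one rule for everything below the primary outcome: "Secondary outcomes will also be analyzed as non-inferiority using 0.5 SD as a non-inferiority margin, but will be tested two-sided". No secondary outcome is excepted, and no other section gives a different margin.

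The Objectives and hypotheses section ends its list of secondary outcomes with "time till recurrence, and survival", and the abstract's list closes with "fear of recurrence, anxiety and depression, information provision, recurrence, and survival". Healthcare use is on both lists too, and Objectives and hypotheses expects it to be lower in the intervention arm.

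The Statistical analysis section also gives the origin of the 0.5 SD figure: "a difference of > 0.5 SD indicates a threshold of discriminant change in health status scores of a chronic illness". The models it names are linear and logistic regression and linear mixed models.

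For event rates, the Background puts recurrence in early-stage disease at 3%, and the Sample size section allows for "patient who die (16%) over five-year follow-up".

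**The concern.** Half a standard deviation is a rule of thumb for scores on a scale. It does not carry over to the other kinds of outcome that the sentence covers.

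- **Time to recurrence and survival.** A censored time has no SD from which a margin could be read, and the article names no effect scale, such as a hazard ratio, on which 0.5 SD could be expressed.
- **Recurrence or death as yes/no.** The SD of a binary variable is large relative to a small risk, so half of it is a very generous margin for a rare safety event.
- **Healthcare use.** The stated hypothesis is a reduction. A non-inferiority test does not address it.

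The experimental schedule reduces surveillance visits from 10–13 to four, so recurrence and survival are where harm would show. A non-inferiority label on either could be read as reassurance about safety. With so few events expected, the trial could not back that up.

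**Working it through.** **Number per arm.** The article gives no numerical margin for recurrence or survival, so none can be reproduced. The sample size fixes the number per arm. With margin 6, SD 14.3, 80% power and one-sided 0.025, 2 × (1.96 + 0.8416)² × (14.3/6)² = 89.2, rounded up to 90 per arm, or 180, as stated. Then 180/(1 − 0.20 − 0.16) = 281.25, rounded up to 282, also as stated. That is 141 per arm.

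**Tolerated limit, risk-difference scale.** Assume SD = sqrt(p(1−p)) at the control risk p, so the margin is 0.5 × SD.
- Recurrence, p = 0.03: SD = sqrt(0.03 × 0.97) = 0.1706; margin 0.0853; limit 0.03 + 0.0853 = 11.5%, or 3.8 times 3%.
- Death by five years, p = 0.16: SD = sqrt(0.16 × 0.84) = 0.3666; margin 0.1833; limit 0.16 + 0.1833 = 34.3%, or 2.1 times 16%.

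**Sensitivity to the scale.** Other ways of expressing 0.5 SD for a binary outcome give these limits:

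| Reading | Recurrence (from 3%) | Mortality (from 16%) |
|---|---|---|
| Logit, odds ratio exp(0.5π/√3) = 2.48 | 7.1% (2.4 times) | 32.1% (2.0 times) |
| Probit shift of 0.5 | 8.4% (2.8 times) | 31.0% (1.9 times) |
| Arcsine, h = 0.5 | 16.9% (5.6 times) | 37.7% (2.4 times) |
| SD at the average of the two arms | 18.5% (6.2 times) | 38.2% (2.4 times) |

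**Chance of a non-inferiority claim.** Take 141 per arm, a two-sided 95% interval and the normal approximation: P = Φ((margin − true difference)/SE − 1.96), with SE = sqrt([p₁(1−p₁) + p₂(1−p₂)]/141). The article does not say which SD applies, so two are shown: the control-arm SD, and the SD at the mean of the two risks (pooled).

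| True risks | SE | Fixed margin | P, fixed | Pooled margin | P, pooled |
|---|---|---|---|---|---|
| Recurrence 3% vs 6% | 0.0246 | 0.0853 | 61% | 0.1037 | 85% |
| Recurrence 3% vs 9% | 0.0281 | 0.0853 | 14% | 0.1187 | 55% |
| Mortality 16% vs 24% | 0.0474 | 0.1833 | 59% | 0.2000 | 72% |

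For the first row with the fixed margin: (0.0853 − 0.03)/0.0246 − 1.96 = 0.29, and Φ(0.29) = 0.61. Exact binomial calculation gives 61%, 17% and 59% (fixed) and 87%, 56% and 72% (pooled).

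**In observed counts.** With 141 per arm and the fixed margins, 9 recurrences against 4, or 35 deaths against 23, would still pass.

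**What the trial can estimate.** Expected recurrences per arm at 3% are 141 × 0.03 = 4.2. The half-width of the 95% interval for the difference is 1.96 × sqrt(2 × 0.03 × 0.97/141) = 0.040, about 4 percentage points.

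**The case against.** The best defence is that the sentence was never meant for clinical events. The article ties 0.5 SD to health status scores, and its detailed no-worse hypotheses name only satisfaction, quality of life, fear of recurrence, anxiety, depression and information satisfaction. If the rule cannot be applied to a time to event at all, the authors presumably did not intend it. This is plausible, but the text does not say so. The sentence says secondary outcomes without limit, and the paragraph after it plans logistic models, so non-continuous outcomes were in view.

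A second objection is that the multiples rest on a conversion the article never makes. This stands: every figure here depends on an assumed SD and scale, which is why the range is shown. No scale tried makes the margin tight.

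A third is that not all 141 per arm will be observed, given "With an expected loss to follow-up of 20% and patient who die (16%) over five-year follow-up we need to include 282 patients". This also stands. With 90 per arm and the fixed margin, the chances fall to 43% for doubled recurrence, 11% for tripled recurrence and 41% for mortality of 24% against 16%.

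Two stronger readings should be resisted. A reader might infer that the trial would usually declare a near-quadrupled recurrence risk or a doubled mortality non-inferior. It would not: a true risk exactly at a fixed margin passes only about 2.5% of the time, and the near-quadrupling belongs to one scale. A reader might also infer that national adoption hangs on such a label. The Discussion's condition is that participants seem representative and that "a reduced follow-up schedule results in a similar patient satisfaction at lower costs, the current guideline will be adapted". Its conclusion speaks of similar satisfaction and outcomes without naming recurrence or survival, and it describes another trial as the one powered for survival. Nothing in the article promises proof of oncological safety.

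**Conclusion.** The point holds as a fault in a stated rule. As written, the 0.5 SD margin covers recurrence and survival. It has no defined meaning for them as times to event. Treated as yes/no outcomes, they would be held to a limit of about 2.4 to 6.2 times the control risk for recurrence and 1.9 to 2.4 times for mortality, depending on the scale. On the risk-difference scale with full follow-up, a doubling of recurrence would more often than not be labelled non-inferior under either choice of SD.

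This rests on the article's 3% and 16% as control risks, on an SD that the article does not define for these outcomes, and on 141 per arm. That the article leaves the source of the SD and the time-to-event model to a fuller document is not part of the finding.

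Severity is moderate: the outcomes are secondary and unpowered, and the primary outcome, its 6-point margin and the sample size are untouched.

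**What to change.** In the Statistical analysis section:

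1. Limit the 0.5 SD non-inferiority margin to the continuous questionnaire scales.
2. Report recurrence and survival as estimates with 95% confidence intervals, for example cumulative incidence and survival curves at 36 and 60 months, with no non-inferiority claim. State that the interval for the recurrence difference is expected to have a half-width of about 4 percentage points.
3. Analyse healthcare use for a reduction, to match the hypothesis in Objectives and hypotheses.

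This changes wording only; design, sample size and data collection stay as they are. The cost is giving up a non-inferiority label on recurrence and survival that the trial could not support.
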